# The Selah study protocol of three interventions to manage stress among clergy: a preference-based randomized waitlist control trial

**DOI:** 10.1186/s13063-021-05845-x

**Published:** 2021-12-09

**Keywords:** Stress, Intervention, Mindfulness, Patient preference, Controlled trial

## Abstract

**Introduction:**

Like many helping professionals in emotional labor occupations, clergy experience high rates of mental and physical comorbidities. Regular stress management practices may reduce stress-related symptoms and morbidity, but more research is needed into what practices can be reliably included in busy lifestyles and practiced at a high enough level to meaningfully reduce stress symptoms.

**Methods and analysis:**

The overall design is a preference-based randomized waitlist control trial. United Methodist clergy in North Carolina will be eligible to participate. The intervention and waitlist control groups will be recruited by email. The interventions offered are specifically targeted to clergy preference and include mindfulness-based stress reduction, Daily Examen, and stress inoculation training. Surveys will be conducted at 0, 12, and 24 weeks with heart rate data collected at 0 and 12 weeks. The primary outcomes for this study are self-reported symptoms of stress and heart rate at week 12 for each intervention compared to waitlist control; the secondary outcome is symptoms of anxiety comparing each intervention vs waitlist control.

**Ethics and dissemination:**

Ethical approval was obtained from the Duke University Campus IRB (2019-0238). The results will be made available to researchers, funders, and members of the clergy community.

**Strengths and limitations of this study:**

While evidence-based stress reduction practices such as mindfulness-based stress reduction (MBSR) exist, a wider variety of practices should be tested to appeal to different individuals.Clergy in particular may prefer, and consequently enact, spiritual practices like the Daily Examen, and individuals such as clergy who spend most of their time thinking and feeling may prefer experiential-based practices like stress inoculation training.If efficacious, the Daily Examen and stress inoculation training practices have high feasibility in that they require few minutes per day.This study is limited by the inclusion of Christian clergy of only one denomination.

**Trial registration:**

ClinicalTrials.gov NCT04625777. November 12, 2020.

## Introduction

Members of helping professions, such as clergy, may be particularly susceptible to the adverse effects of chronic stress, particularly chronic work-related stress. Observational evidence reported by more than 1000 United Methodist clergy in North Carolina indicated that clergy exhibit high prevalence rates of chronic disease, including diabetes (12.7%), hypertension (36.2%), asthma (13.8%), and joint-related disease (33.8%), as well as obesity (41.2%) [1]. Further, in a sample of more than 1700 United Methodist clergy, clinically relevant symptoms of depression measured using the Patient Health Questionnaire-9 were reported by 11.1%, which is significantly higher than the adjusted national average of 5.5% [2]. The prevalence of clergy meeting the criteria for clinically relevant anxiety using the Hospital Anxiety and Depression Scale was also elevated at 13.5% [2]. The high prevalence of physical and mental health issues among clergy may be due in part to stressors from an emotionally demanding occupation with little respite.

One prominent theory of stress is the job-demand-control-support (JDCS) model [3], which indicates that stressful jobs are those characterized by high demand, low control, and low perceived support [4]. Clergy perform a wide variety of skilled roles, including inspiring the congregation, providing one-on-one care for congregants, performing sacraments, educating congregants, overseeing educational programming, and leading social justice activities. The work week typically averages 50 h or more with the expectation of being on call around-the-clock [5, 6]. While certain tasks such as preaching are predictable, clergy have no control over the timing of funerals and congregant crises, and only a variable degree of control over congregant perception and criticism of the direction that the clergy are taking the congregation. In terms of support, clergy experience work-related support to varying degrees; they direct a volunteer workforce and often do not receive the support needed to match the tasks or the emotional challenges faced [7].

Approaches to stress management can be categorized as *individual-level* or *organizational-level* depending on their target audience [8]. Numerous individual-level approaches have been developed to manage stress, such as cognitive-behavioral therapy, mindfulness, exercise, and relaxation. Meta-analyses report medium to large effect sizes for cognitive-behavioral approaches [9] and small to medium effect sizes for mindfulness- and relaxation-based approaches [9–11] to stress management. Learning to manage stress can be viewed as skill acquisition requiring engagement and practice. As such, choosing an intervention that individuals are willing and motivated to practice is a key consideration [12]. We sought to develop interventions that are tailored to the job demands and preferences of clergy in order to improve engagement and reduce the chronic negative impact of stress.

Our team conducted a pilot study with clergy to evaluate the feasibility and acceptability of four potentially stress-reducing interventions while taking participant preference into account. Three stress-reducing interventions showed promising trends in improving self-reported stress and/or physiological markers of parasympathetic nervous system activation. This manuscript reports the trial protocol for a waitlist-controlled preference design to evaluate the three interventions that were promising: mindfulness-based stress reduction, the Daily Examen, and a set of stress inoculation skills that we entitle stress proofing.

The goal of the Selah study is to test the efficacy of each of three flexible and scalable stress management interventions among clergy who serve in a high-stress occupation. The approaches of the three interventions differ; by determining whether each intervention is superior to no treatment on stress symptoms, anxiety symptoms, and heart rate variability, study findings will indicate evidence-based program options for clergy, based on their preferences.

## Methods

### Research objectives

#### Objective 1

To compare the impact of, separately, MBSR, the Daily Examen, and stress proofing with a waitlist control condition, on stress outcomes at 12 weeks.

Hypotheses 1 and 2: When randomly assigned to waitlist vs non-waitlist, MBSR, the Daily Examen, and/or stress proofing will be superior to the waitlist control on stress symptoms (hypothesis 1) and HRV (hypothesis 2) at 12 weeks (co-primary outcomes).

#### Objective 2

To compare the impact of, separately, MBSR, the Daily Examen, and stress proofing with a waitlist control condition, on anxiety symptoms at 12 weeks.

Hypothesis 3: When randomly assigned to waitlist vs non-waitlist, MBSR, the Daily Examen, and/or stress proofing will be superior to the waitlist control on anxiety symptoms at 12 weeks (secondary outcome).

#### Objective 3

To compare the impact of, separately, MBSR, the Daily Examen, and stress proofing with a waitlist control condition, on stress and anxiety symptoms at 24 weeks.

Hypotheses 4 and 5: When randomly assigned to waitlist vs non-waitlist, MBSR, the Daily Examen, and/or stress proofing will be superior to the waitlist control on stress symptoms (hypothesis 4) and anxiety symptoms (hypothesis 5) at 24 weeks (exploratory outcomes).

#### Objective 4

To determine whether having a preference, and that preference being honored, was associated with better outcomes on stress symptoms, HRV, and anxiety symptoms.

Hypotheses 6–8: Participants who had a stated preference and received that intervention (i.e., MBSR, the Daily Examen, and stress proofing combined) will experience larger between-arm (waitlist vs non-waitlist) differences in improvements on stress symptoms (hypothesis 6), HRV (hypothesis 7), and anxiety symptoms (hypothesis 8) at 12 weeks when compared to no-preference participants randomly assigned across interventions and waitlist (exploratory outcomes).

### Study design: partially randomized waitlist-controlled preference trial

This study’s timing crossed the start of the COVID-19 pandemic, which necessitated changes in the original design registered with clinicaltrials.gov (see Fig. 1). In this manuscript, we report the pandemic-adapted design (see Fig. 1), a partially randomized waitlist-controlled preference trial with assignment into non-waitlist (i.e., intervention) vs waitlist arms. Preference-based trials are a kind of pragmatic clinical trial design that recognizes individuals have treatment preferences that are likely to affect the outcomes and result in “preference effects” [12]. These preference effects may be due to expectancy effects or degree of engagement, which are particularly important in behavioral interventions. In conventional randomized controlled trials, participant choice is removed to create high internal validity between the intervention and treatment effects [13]. Blinding participants to the allocated intervention can be challenging in behavioral trials, making participant preferences more salient.

**Fig. 1 Fig1:**
[figure not shown]
Pandemic-adapted Selah study design: a partially randomized waitlist-controlled preference

We enacted a partially randomized preference design to assign participants to particular interventions [12]. Prior to March 1, 2020, and the COVID-19 pandemic, participants read the descriptions of the three stress management interventions and provided preference ratings using the Treatment Acceptability and Preferences Scale [14] to help them think through their preferences. In addition, participants were asked whether they preferred any of the three interventions or if the interventions were equally appealing to them (i.e., no preference). Those with a preference were asked whether they had one or two equal first choices. Participants who preferred one intervention were assigned to their preferred intervention and randomized to a non-waitlist vs waitlist condition; the waitlist condition participants provide control data prior to intervention receipt. Upon completing the waitlist condition, participants were allowed to update their preference and receive their currently preferred intervention while providing data. Participants who stated no preference (or equally preferred two interventions over the third) were randomized to receive one of three (or, if applicable, two) interventions in a non-waitlist condition or to the waitlist condition (Fig. 1).

During a time of heightened stress due to COVID-19, stress reduction research seemed particularly important, and we sought more participants to maximize statistical power should others withdraw [15]. For those reasons, after March 1, 2020, we continued to recruit participants and assigned them to their preferred intervention in a non-waitlist condition (Fig. 1). These additional recruits will provide observational, as-treated data.

### Study setting

Clergy from the United Methodist Church (UMC) appointed to positions in North Carolina (NC) will be recruited. There are approximately 1600 active UMC clergy in this potential study group. The majority serve as congregational leaders, but some work in non-profit and denominational settings in rural, suburban, and urban environments. The average age is 53, 66% are men, and 90% are white and non-Hispanic [16].

### Patient and public involvement

The material introduced in the interventions was pilot-tested by 78 clergy prior to the final development of the intervention protocols.

### Participant eligibility

#### Inclusion criteria

Participants must have had a current appointment in the 2019–2020 or 2020–2021 appointment cycle of the NC Annual Conference or the Western NC Annual Conference of the UMC to be included in the study. Participants are eligible if they are 18 years of age or older and willing to participate in the survey and HRV data collection and commit to completing their assigned stress management intervention. There are no stress- or health-related inclusion criteria.

#### Exclusion criteria

In an attempt to increase ecological validity, no exclusion criteria were set for participation in the trial. Participants with underlying medical conditions which could seriously impact the integrity of their HRV data were excluded from HRV data collection, including a diagnosis of tachycardia; being pregnant or becoming pregnant during the course of data collection; being diagnosed with COVID-19; having a pacemaker; and documentation of other cardiovascular-related chronic or acute morbidities.

### Procedures

#### Screening, recruitment, and enrollment

Recruitment is expected to benefit from the 12-year partnership that the Duke Clergy Health Initiative and the two UMC conferences in NC have enjoyed. Participants will be recruited primarily via email addresses provided by the denomination. Additionally, all eligible clergy will receive a program brochure in the mail. Study staff, including a recruitment coordinator who is well-known to the population, will promote the study and answer questions at in-person gatherings. Participants will be directed to the study website (spiritedlife.org) to learn more about the interventions and study details. The web-based registration form will guide participants through a series of questions that will culminate in indicating their preferred intervention(s) and study consent. Participants will be compensated $20 for each of the first two surveys and $25 for the final survey, as well as $25 for each occasion of heart rate tracking submitted (possible total = $115).

#### Allocation concealment mechanism

In the current study, the consideration for allocation concealment was concealing assignment to waitlist vs non-waitlist. Participants enrolled prior to assignment; therefore, knowledge of waitlist vs non-waitlist allocation by study staff or participants was not possible at the time of enrollment.

#### Randomization and blinding

For participants recruited before March 1, 2020, after enrollment, participants were randomly allocated to waitlist vs non-waitlist using computer assignment. The analysis statistician wrote the randomization codes in Stata version 16. The allocation sequence generation used stratified randomization, stratifying based on intervention preference (see Table 1). Random assignment to an intervention type was performed using a random draw from a uniform distribution. Random assignment to immediate vs waitlist condition was performed by drawing a random sample from a list of participants within each intervention type assignment. To keep the analysis statistician blinded, a research staff member ran the Stata program and gave the assignment information to trial coordinators who then coordinated logistics. Trial coordinators had no prior knowledge of potential assignment to waitlist vs non-waitlist at the time of recruitment or enrollment. Table 1 reports assignment and randomization allocations for each preference scenario. Preference data were collected before allocation, and baseline data (e.g., on stress and anxiety symptoms) were collected after allocation. A secondary recruitment period was initiated after March 1, 2020, that did not include random assignment; data from those participants will be included in a secondary as-treated analysis. The analysis statistician will be blinded to the intervention allocation. It is not possible to blind participants, interventionists, or outcome assessors.

**Table 1 Tab1:** Study assignment approach for each preference and enrollment date scenario

Preference scenario	Assignment approach

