#### Study arms: non-waitlist interventions and waitlist

This trial includes three non-waitlist study arms (mindfulness-based stress reduction, Daily Examen, and stress proofing) and one waitlist arm that includes two conditions: first providing control data and then participating in any intervention condition. Originally, participants were to be trained in small workshop formats delivered across NC between April 2020 and May 2021. Due to the global pandemic, all workshops were converted to online delivery formats and delivered during the same anticipated months. Interventions will be delivered in small groups of 10–25 participants. Survey data will be collected online, and HRV data will be collected by the participants in their respective personal settings.

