#### Heart rate

A subset of participants will be provided with an ambulatory heart rate monitoring device to wear for a 48-h period during week 0 and week 12, during which time participants proceeded with their usual daily routines, including exercising, bathing, and sleep activities.

Heart rate will be measured using continuous electrocardiographic (ECG) recording sampled at a rate of 1000 Hz and used to calculate *heart rate variability*. Participants will be fitted with an eMotion Faros 180 ambulatory heart rate recording device (Bittium) connected by electrode leads to two pre-gelled (Ag/AgCl) disposable Ambu BlueSensor wet-gel ECG electrodes attached beneath the right clavicle and left ribcage. The 48-h ECG recording will be imported to the Kubios HRV Premium V3.4.1 software [24], partitioned into 5-min segments, visually inspected to allow for manual correction of ectopic beats, detrended, and subject to Kubios’ automatic artifact correction algorithm [25]. Heart rate variability will be indexed using the time-domain metric *root mean square of successive RR differences* (*RMSSD*) given that it is less affected by breathing and a better suitable outcome measure in ambulatory studies than frequency-domain measures [26].

Following recommendations for the detection of circadian rhythmicity [27], 5-min segments across 24 h of recording will be subject to a cosinor analysis using the Cosinor package for R. Two individual-level cosine function parameters will be estimated by linear models with ordinary least square estimations to quantify the circadian variability parameters: (i) midline estimating statistic of rhythm (MESOR), defined as the rhythm adjusted 24-h mean, and (ii) amplitude, defined as the distance between MESOR and the maximum of the cosine curve (i.e., half the extent of rhythmic change in a cycle).

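### The blanket statement that outcome assessors cannot be blinded does not hold for the co-primary HRV outcome, and the article does not say whether ECG correction was masked

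*Protocol article*

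**What the plan says.** All references are to the protocol article.

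- **Randomization and blinding.** The article says "It is not possible to blind participants, interventionists, or outcome assessors", with no exception by outcome. It then gives the protection at the analysis stage: "The analysis statistician will be blinded to the intervention allocation".
- **Research objectives, Objective 1.** Stress symptoms and HRV at 12 weeks are co-primary.
- **Heart rate.** "The 48-h ECG recording will be imported to the Kubios HRV Premium V3.4.1 software". The recording is cut into 5-minute segments, which are "visually inspected to allow for manual correction of ectopic beats, detrended, and subject to Kubios’ automatic artifact correction algorithm". "Heart rate variability will be indexed using the time-domain metric" RMSSD, the root mean square of successive RR differences.
- **Study arms.** "HRV data will be collected by the participants in their respective personal settings".
- **Waitlist condition.** Eligible waitlist participants give the same 48-hour recording at weeks 0 and 12.
- **Primary outcomes and Secondary outcome.** C-SOSI and GAD-7 are both self-reported.
- **Data management.** Data are de-identified and stored securely. Nothing is said about hiding arm or visit from whoever processes the ECG.

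**The concern.** The article treats assessor blinding as impossible across the board, although one of its two primary outcomes has an assessment step that can be masked. HRV is the only primary or secondary outcome that is not self-reported. The self-reported outcomes come from participants who know whether they are on the waitlist, so HRV is the natural check on expectancy effects in those scales. Its value as a check depends partly on the ECG being handled the same way in every arm.

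Deciding which beats are ectopic, and correcting them by hand, is a judgement. RMSSD is built from squared differences between successive beats, so it responds to such decisions. If the person editing knows the arm or the visit, a systematic difference in editing could enter the arm comparison. Blinding the statistician does not remove it, because the edited values already exist when the analysis starts.

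**Working it through.** **1. The plan's own HRV figure.** The only number tied to this outcome is the sample size of 140 per arm (Power analysis), and it reproduces.

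- Inputs: effect size 0.50, alpha 0.0167 (taken as two-sided), power 0.80, design effect 1.3, loss to follow-up 20%.
- Two-sample t-test: 86 per arm (power 0.804).
- Design effect: 86 × 1.3 = 111.8.
- Loss to follow-up: 111.8 / 0.80 = 139.75, rounded up to 140.

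The sample size is not in dispute. It gives the effective size used in step 3.

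**2. The statement set against each outcome.**

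| Outcome | Who produces the value | Is assessor blinding impossible? |
|---|---|---|
| C-SOSI (co-primary) | Participant, online survey | Yes |
| GAD-7 (secondary) | Participant, online survey | Yes |
| HRV (co-primary) | Recorded by the participant, then inspected and corrected in software | Not for the inspection and correction |

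Three features of the article show that the HRV step can be masked:

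- Participants make the recording in their own settings, so the person reading it need not meet them.
- Intervention and waitlist participants give the same type of recording at the same two time points, so the format does not reveal the arm.
- The trial already separated roles for the statistician's sake: a staff member ran the allocation program and passed assignments to the coordinators.

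The general statement is therefore wrong for this step. Two things remain unstated: who performs the correction, and whether that person knew arm or visit. De-identification of stored data answers neither, because a file without a name can still carry an arm or visit label.

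**3. What a bias would do, if there were one (illustration only).** Suppose there is no true effect and differential editing shifts the arm difference by b standard deviations. The effective size per arm is 140 × 0.80 / 1.3 = 86.2, and the noncentrality of the t-test is b × √(86.2 / 2) = 6.56b. At nominal two-sided alpha 0.0167:

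| Assumed shift b (SD) | Noncentrality | Rejection rate with no true effect |
|---|---|---|
| 0 | 0 | 0.0167 |
| 0.05 | 0.33 | 0.023 |
| 0.10 | 0.66 | 0.042 |
| 0.20 | 1.31 | 0.138 |

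The values of b are assumptions. Nothing in the article indicates which applies, and zero is possible.

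**The case against.** **The sentence may concern only the surveys.** Most outcomes here are online questionnaires, and the article never says that ECG processors count as outcome assessors. On that reading the wording is loose, and ECG handling is the sort of detail a condensed article leaves to the full protocol. This stands in part: unmasked reading is not established. But the article does more than leave the matter out. It asserts that assessor blinding is impossible, without exception, while naming HRV as co-primary and describing a manual correction step.

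**Automatic correction also applies.** The same sentence of the Heart rate section adds Kubios' automatic artifact correction. This stands. A gross ectopic beat missed by hand may still be caught.

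**A reader might infer a specific and sizeable bias.** For example, take a 5-minute segment at 60 beats per minute with RMSSD 30 ms. It has 299 successive differences, with sum of squares 299 × 900 = 269,100. One uncorrected beat 300 ms early, with a full compensatory pause, replaces three ordinary squared differences (2,700) by 300² + 600² + 300² = 540,000. RMSSD becomes √(806,400 / 299) = 51.9 ms. If arms differed by one such beat in 5% of segments, the mean would shift by 0.05 × 21.9 = 1.1 ms. With an SD of 15 ms that is 0.07 SD, about 15% of the planned 0.50.

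The arithmetic is right, but the documents do not support the inference. The heart rate, RMSSD, SD, prematurity and 5% are all assumed, and the example lets the beat escape automatic correction. If the algorithm caught half of such beats the shift would be about 0.04 SD; if it caught 90%, about 0.007 SD. The difference would also have to run consistently in one direction by arm; inconsistency unrelated to arm adds noise rather than bias.

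**Data collection is over.** It ended on September 24, 2021 (Trial status). Coding files can then protect only recordings not yet edited, so the remedy must also cover those already done.

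**Conclusion.** The point holds as a wrong statement in the article together with an undisclosed masking status. Assessor blinding is impossible for C-SOSI and GAD-7 but possible for the inspection and manual correction of ECG recordings that feed a co-primary outcome. This rests on the text alone, plus the inference that someone other than the participant edits the recordings. The article does not say so, but the described software processing makes it very likely.

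The size of any bias is unknown and may be small. A reader might conclude that HRV was in fact edited unmasked, or that the HRV result is distorted by a stated fraction of the planned effect. The article supports neither conclusion: the editor's identity and masking are not given, and no figure in it bears on how editing might differ by arm. Masking the editor would also leave untouched any change in how unblinded participants behave while wearing the device.

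The correction is still worth making, because it is cheap and protects the one outcome that does not depend on self-report.

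**What to change.** 1. In Randomization and blinding, limit the impossibility statement to participants, interventionists and self-report outcomes.
2. Add that ECG inspection and correction are done on files under a code that hides arm and visit (week 0 or week 12), with editing locked before the code is linked to allocation.
3. If any recordings were edited without masking, say so and report a sensitivity analysis of HRV using automatic artifact correction only, beside the main result.
4. If editing was in fact masked throughout, say that; the sentence as it stands would then misreport the trial's conduct.

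**Cost.** Items 1 and 4 are text. Item 2 needs a coded file list for recordings not yet edited. Item 3 means reprocessing stored recordings without the manual step and running the HRV model once more. No new participant procedure or visit is needed.
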